## Abstract

**Background:**

Patient satisfaction is an important metric of health-care quality. Accidental awareness under general anaesthesia (AAGA) is a serious complication of anaesthesia care which may go unrecognised in the immediate perioperative period but leads to long-term psychological harm for affected patients. The SNAP-1 study aimed to measure patient satisfaction with anaesthesia care and the incidence of AAGA, reported on direct questioning within 24 h of surgery, in a large multicentre cohort. A secondary aim of SNAP-1 was to test the effectiveness of a new network of Quality Audit and Research Coordinators in NHS anaesthetic departments, to achieve widespread study participation and high patient recruitment rates. This manuscript describes the study methodology.

**Methods:**

SNAP-1 was a prospective observational cohort study. The study protocol was approved by the National Research Ethics Service. All UK NHS hospitals with anaesthetic departments were invited to participate. Adult patients undergoing any type of non-obstetric surgery were recruited in participating hospitals on 13th and 14th May 2014. Demographic data were collected by anaesthetists providing perioperative care. Patients were then approached within 24 h of surgery to complete two questionnaires—the Bauer patient satisfaction questionnaire (to measure patient reported outcome) and the modified Brice questionnaire (to detect possible accidental awareness). Completion of postoperative questionnaires was taken as evidence of implied consent. Results were recorded on a standard patient case report form, and local investigators entered anonymised data into an electronic database for later analysis by the core research team.

**Results:**

Preliminary analyses indicate that over 15,000 patients were recruited across the UK, making SNAP-1 the largest NIHR portfolio-adopted study in anaesthesia to date. Both descriptive and analytic epidemiological analyses will be used to answer specific questions about the patient perception of anaesthesia care overall and in surgical sub-specialties and to determine the incidence of AAGA.

**Conclusions:**

The SNAP-1 study recruited a large number of UK hospitals and thousands of perioperative patients using newly established networks in the UK anaesthetic profession. The results will provide benchmarking information to aid interpretation of patient satisfaction data and also determine the incidence of AAGA reported on a single postoperative visit.

**Electronic supplementary material:**

The online version of this article (doi:10.1186/s13741-015-0011-2) contains supplementary material, which is available to authorized users.

## Background

Patient feedback metrics are viewed as important assessments of the quality of health care. Broadly, the patient’s viewpoint can be sought in three domains. First, they can provide feedback on interactions with health-care professionals and specifically communications skills: colloquially, this might be referred to as the “bedside manner” test; and in the UK, this is a mandatory assessment for clinical doctors as part of the revalidation process. Second, patients can provide feedback on their *experience* of health care; such questionnaires would usually seek the patient viewpoint on a diverse range of issues such as cleanliness of the care environment, efficiency of treatment and services and the courtesy and trustworthiness of staff. Finally, patients may provide their views on the efficacy of their treatment, using patient-reported outcome measures (PROMs). The National Health Service (NHS) has a mandated programme of patient-reported outcome measures for a number of surgical procedures which are aimed at alleviating symptoms and improving health-related quality of life, such as hip and knee joint replacement and varicose vein repairs.

In perioperative anaesthesia practice, the patient perspective on their care can be sought through the administration of patient satisfaction measures. Patient satisfaction has been previously described as a construct which comprises a cognitive evaluation and an emotional response to the care received [1]. It is important to use an appropriately designed questionnaire to measure patient satisfaction, so that reliable and valid results are obtained. A systematic review has recently been published which qualitatively assessed the psychometric development and validation of published patient satisfaction questionnaires relating to anaesthesia practice [2]. This study concluded that the Bauer questionnaire [3] was amongst the best for use in the perioperative setting, both in terms of the rigour with which it was developed and the acceptability of the questionnaire to patients.

While it is of clear importance to measure patient experience and satisfaction, in anaesthetic practice, an important adverse outcome which is not commonly searched for or reported in routine practice is accidental awareness under general anaesthesia (AAGA). Estimates of the incidence of AAGA vary from 1–2 per 1,000 patients in clinical trials, [4-6] to considerably lower (approximately 1 in 15,000 or 20,000 general anaesthetics) in observational studies and surveys [7-9]. As with patient satisfaction, of paramount importance in being able to estimate the incidence of AAGA is the type of questionnaire or interview administered to patients. Traditionally, the Brice questionnaire and protocol has been adopted to elicit reports of AAGA—a series of five open-ended questions which are administered to the patient three times within 30 days of surgery [10]. A modified Brice questionnaire, which used closed questions with multiple choice answers, was subsequently adopted for a large randomised control trial evaluating the efficacy of a protocoled use of Bi-spectral Index monitoring in the prevention of AAGA [6].

While most anaesthetists will be aware of the availability both of patient satisfaction questionnaires and Brice methods, clinical experience tells us that they are infrequently used in routine practice in the United Kingdom (UK). Reasons for this may include a lack of familiarity with validated measures and a lack of benchmarking data to aid interpretation of patient satisfaction data. Furthermore, there are only limited data evaluating the reported incidence of AAGA where patients have been approached using a Brice-style questionnaire in a real-world setting. Therefore, the first UK Sprint National Anaesthesia Project (SNAP-1) aimed to prospectively measure patient reported outcome after anaesthesia in a large multicentre cohort. This paper describes the methods and analysis plan for the SNAP-1 study.

## Methods

### Aims and objectives

The aims of SNAP-1 are to report the descriptive and analytic epidemiology of the delivery and patient-reported outcomes of anaesthesia in the UK. Objectives are as follows:To describe conduct of perioperative anaesthesia in the UK, including personnel, technology support and pharmacological management and postoperative resource utilisation;To describe the characteristics of the patient population undergoing surgery involving an anaesthetist;To measure patient satisfaction after anaesthesia using a validated survey on a national scale;To determine the relationship between individual patient predicted risk using validated scoring systems and patient-reported postoperative outcomeTo record the reported incidence of AAGA in routine UK practice using a modified Brice questionnaire administered within 24 h of surgery;To determine associations between patient characteristics, procedural factors and adverse patient-reported outcomes

In addition to these main aims and objectives, a secondary aim of SNAP-1 is to determine the effectiveness of the Quality Audit and Research Coordinator (QuARC) network, at achieving local engagement and coordination with a national research project. The QuARC network was established by the National Institute for Academic Anaesthesia’s Health Services Research Centre (NIAA HSRC); all UK anaesthetic departments were asked to nominate a consultant anaesthetist as the QuARC, with the aim of liaising between the clinical department and the NIAA HSRC in national survey, audit, quality improvement and research projects. A particular aim of SNAP-1 was also to engage trainee anaesthetists in research. Previous surveys have shown that many trainees are unable to access opportunities to participate in research, despite a desire to do so; [11,12] therefore, SNAP-1 was proposed as an opportunity to address this gap.

### Study design and ethics

SNAP-1 was a multicentre observational study. Ethics approval was granted by the UK National Research Ethics Service (West Midlands Committee; REC reference 14/WM/0043). The study was approved as a research study, with implied consent being provided by patients upon completion of the questionnaires.

### Recruitment, inclusion and exclusion criteria

All adult (≥18 years) patients in participating hospitals undergoing any type of surgery or procedure under anaesthesia (local, regional or general) or sedation administered by an anaesthetist were eligible for inclusion. The following patient groups were excluded:Age less than 18 yearsPatients unable to understand spoken or written EnglishObstetric patientsPatients too unwell or confused to be able to complete the questionnairePatients who refused consent

The recruitment dates for SNAP-1 were 13 and 14 May 2014. All eligible patients having procedures involving an anaesthetist in participating on those dates were given a participant information sheet (Additional file 1) before their procedure, explaining that they would be approached postoperatively to complete the study questionnaires. No specific consent form was required as the ethics approval stated that completion of the follow-up questionnaires could be taken as implied consent: this was explained to patients in the participant information sheet. The target recruitment rate for the study was 7,500 patients.

### Dataset

The dataset comprised three questionnaires: a demographic questionnaire (completed by the perioperative anaesthetist at the time of surgery; Additional file 2), the Bauer patient satisfaction questionnaire and a modified Brice questionnaire (MBQ) (Additional file 3). The MBQ was adapted from that used in the BAG-RECALL study [6]. Demographic data were collected on all patients in participating centres who met inclusion criteria on the study days. The variables within the demographic questionnaire included patient factors, personnel factors and process factors. The patient risk variables were based on simple previously validated preoperative predictors of objective adverse postoperative outcomes. Patients were subsequently approached to complete the follow-up questionnaires (see Additional file 3) either on the day of surgery before hospital discharge (for ambulatory surgery patients) or within 24 h of surgery (for those undergoing inpatient surgery). Both the date of the procedure and the date of survey completion were noted for each patient. Data were collected on paper case report forms (CRFs) and subsequently transcribed by local investigators into electronic CRFs via a secure web-based data entry portal. A unique identifier for each case was generated through the creation of each new eCRF.

### Data management

The paper CRFs include fields for patient identifiers (name, date of birth and hospital number). These CRFs are securely stored at each participating site in accordance with the principles of information governance and good clinical practice. The electronic CRFs did not contain fields for patient identifiable information: therefore, each local investigator was required to keep a recruitment log to enable later identification of patients if required. Thus, no patient identifiable data was transferred outside the local hospital environment either electronically or on paper.

### Post-study investigator questionnaire

In order to assess the impact of this study on engagement with research amongst UK anaesthetists, a post-study questionnaire was issued to all registered investigators (see Additional file 4).

### Study coordination and funding

Investigators were sought from every anaesthetic department in the UK which provided perioperative services to adult non-obstetric patients. Site and investigator recruitment was facilitated through the Quality Audit and Research Coordinator (QuARC) network. Recruitment of trainee investigators was particularly encouraged. SNAP-1 was also adopted onto the National Institute for Health Research clinical research portfolio, thereby enabling Clinical Research Network support to be provided to participating hospitals.

Study management was led by a core group of investigators based at the UCL/UCLH Surgical Outcomes Research Centre and the NIAA’s HSRC. The core group consisted of the Chief Investigator, a trainee lead investigator and a study administrator based at the NIAA HSRC. Study oversight was provided by the Executive Management Board of the NIAA’s HSRC. The study sponsor was the University College London Hospitals NHS Foundation Trust. The study was funded through a grant of £18,069 from the National Institute for Academic Anaesthesia and through salary support (for the Chief Investigator and trainee lead investigator) from the University College London Hospitals NHS Foundation Trust and its National Institute for Health Research Biomedical Research Centre.

### Analysis plan

All results will be reported in accordance with the “Strengthening the Reporting of Observational Studies in Epidemiology” (STROBE) statement [13]. The main focus of analysis is to describe the epidemiology of the practice of anaesthesia and patient-reported outcome after anaesthesia in the overall cohort and, where feasible, in surgical sub-specialty groups and for specific surgical procedures.

#### Study recruitment and missing data

Study recruitment rates and missing data will be reported. The total number of sites that participated (broken down by country) will be presented in addition to the total number of patients recruited. The number of eligible patients who did not complete the questionnaires and the reasons reported for this will be stated. Comparison will be made of the demographics of patients who did and did not complete follow-up questionnaires. A description will be provided of any missing data points.

#### Descriptive epidemiology

The information collected from the patient demographic and perioperative questionnaire will be presented. The number of cases per specialty and type of procedure will be stated. Point estimates and ranges will be given for patient descriptors (for example, age, ASA grade, comorbidities and body mass index) in addition to detail of the use of long-term analgesics or benzodiazepines. The characteristics of surgery will be described by urgency, severity and length of operation. The personnel (i.e. seniority of the anaesthetist(s)) involved will be described as well as the type and site of anaesthesia induction. Anaesthetic technique and postoperative destination will be described and summarised both overall and for surgical sub-specialty groups.

The variables for three risk prediction/adjustment tools were included in the dataset: the population-based ASA grade; [14] the Surgical Risk Scale; [15] and the Surgical Outcome Risk Tool [16]. The latter two of these systems have been validated for the prediction of 30-day mortality after surgery. The predicted mortality based on these scoring systems will be presented for the overall patient population and for surgical sub-specialty groups. Data will be presented describing patterns of admission to high dependency or intensive care facilities compared with the predicted risk of 30-day mortality according to these systems, in order to assess compliance with national recommendations on postoperative care [17,18].

#### Bauer patient satisfaction questionnaire

For each of questions 1–10 (on anaesthesia-related discomfort), counts and percentages will be reported for each of the three potential responses. For questions 11–15 (which ask about satisfaction with anaesthesia care), counts and percentages of each of the four potential responses will be reported. Further analysis of the all these responses within different categories using chi-square testing with Bonferroni’s correction to compare outcomes between categories, such as (for example):Ambulatory surgery—comparisons by specialty and operative procedureInpatient surgery—comparisons by specialty and operative procedureElective/expedited versus immediate/urgent

Within surgical categories, comparison will be made between the responses to the patient satisfaction questionnaires depending on whether the questionnaire was administered on the day of surgery or day 1 postoperatively.

Univariate analysis will be used to demonstrate associations between patient factors and adverse outcomes, defined as the worst category answer for each question. Logistic regression will be used to determine independent risk factors for the adverse outcomes. Analyses will be conducted for the overall population and for surgical and patient categories where the sample size allows. The decision on whether to conduct regression analyses in particular subgroups will be informed by consideration of the principles described by Vittinghoff and McCulloch, including consideration of whether continuous or binary variables are included, the number of events per outcome variables and the sample size itself [19].

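### The chi-square comparisons of the Bauer items use single-step Bonferroni, which is valid; Holm's step-down procedure over the same tests would keep the same error guarantee with somewhat more power.

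*Protocol article*

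**What the plan says.** The section of the protocol article on the Bauer questionnaire first sets out description. For the discomfort items: "For each of questions 1–10 (on anaesthesia-related discomfort), counts and percentages will be reported for each of the three potential responses". For the satisfaction items: "For questions 11–15 (which ask about satisfaction with anaesthesia care), counts and percentages of each of the four potential responses will be reported". That makes 10 + 5 = 15 items.

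It then plans further analysis of these responses "using chi-square testing with Bonferroni’s correction to compare outcomes between categories". Three lines of examples follow, introduced by the words "correction to compare outcomes between categories, such as (for example": ambulatory surgery by specialty and by procedure, inpatient surgery by specialty and by procedure, and elective or expedited against immediate or urgent surgery. A separate sentence adds a comparison within surgical categories "depending on whether the questionnaire was administered on the day of surgery or day 1 postoperatively".

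The article gives no alpha, number of tests or simultaneous confidence intervals for these comparisons. Under Analysis plan it states the priority: "The main focus of analysis is to describe the epidemiology of the practice of anaesthesia and patient-reported outcome".

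**The concern.** Bonferroni holds every test to the same threshold, alpha divided by the number of tests, however many hypotheses have already been rejected. Holm starts at that threshold and relaxes it after each rejection. A set of tests with many real differences is where the relaxation pays, and differences between surgical specialties in discomfort or satisfaction could well be numerous. The article hopes its results will inform patient leaflets for different types of surgery and serve as benchmarks, so these comparisons have a practical use.

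At stake is a modest number of real differences that would be reported as non-significant although a procedure with the same error guarantee would have detected them.

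**Working it through.** The article states no threshold, divisor or power for these tests, so there is no figure to reproduce. The check compares the two procedures under stated assumptions.

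**Inputs**
- Items: 15 (article, Bauer section).
- Comparisons: the examples give 2 settings × 2 groupings + 1 urgency contrast = 5, each taken as one global test. Counting them this way is an assumption.
- Number of tests: m = 15 × 5 = 75, for illustration only.
- Familywise alpha: 0.05, two-sided (assumed).
- Power per real effect under Bonferroni: 70% or 80% (assumed).

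**Thresholds**
- Bonferroni: every p-value is compared with 0.05/75 = 0.00067.
- Holm: the p-values are ordered. After r rejections the next one is compared with 0.05/(75 − r), and testing stops at the first failure. This gives 0.05/75 = 0.00067 for the smallest, 0.05/50 = 0.001 after 25 rejections, 0.05/25 = 0.002 after 50, and 0.05/10 = 0.005 after 65.

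No Holm threshold is below 0.05/75, so every Bonferroni rejection is also a Holm rejection. Holm's error guarantee needs no assumption about dependence, which matters because the 15 items come from the same patients.

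**Simulated power per real effect** (75 independent two-sided z tests, 20,000 repeats)

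| Real effects among 75 | Holm, when Bonferroni has 70% | Holm, when Bonferroni has 80% |
|---|---|---|
| 10 | about 71% | about 81% |
| 25 | 72.5% | 82.2% |
| 50 | 76.4% | 85.9% |
| 65 | 80.5% | 89.6% |

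The gains are about 1, 2, 6 and 10 points down the rows. Holm's familywise error stayed below 5% in these settings, and no Bonferroni rejection was lost.

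**Sensitivity** (separate simulation, 10,000 repeats, 80% power under Bonferroni)
- Correlation of 0.3 between tests, m = 75: 80.1% becomes 81.2% with 20% of effects real, 80.3% becomes 83.8% with 50% real, and 79.9% becomes 86.9% with 80% real.
- Different m, independent tests, 50% real: 80.0% becomes 84.2% at m = 15 and 83.7% at m = 150.
- No real effects: Holm and Bonferroni have identical familywise error, so nothing is gained or lost.

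The gain therefore depends on the share of real effects far more than on the number of tests.

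**Pairwise contrasts.** One might hope to save further power by testing specialties pairwise, unadjusted, once a global test is significant. This was simulated for one item with 15 assumed specialties of 1,000 patients, one truly different (20% against 7%) and 14 identical. The global test passed at 0.05/75 in every run. Unadjusted pairwise tests at 0.05 then gave at least one false positive among the 14 identical specialties in 79% of runs. Pairwise contrasts must be counted in the Holm procedure.

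**The case against.** The strongest objection is that nothing here is wrong. Bonferroni is valid under any dependence, easy to explain and conservative, so preferring Holm is an improvement and not a correction. That stands, and it limits the weight of the point.

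The gain is also small unless many effects are real: with 10 of 75 real it is about 1 point. The 70 to 80% starting power comes from no figure in the article. The article states "Preliminary analyses indicate that over 15,000 patients were recruited across the UK", but this does not fix the power of any one comparison. Both remarks stand.

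Holm also gives up Bonferroni's simple matching simultaneous intervals, a real loss where estimation comes first. It weighs little here, since the article plans no such intervals for these comparisons. Counts and percentages for every response are reported whatever the tests show, so no difference is concealed from the reader.

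A stronger reading is tempting. Because the comparisons are introduced as examples and recruitment had finished, a reader might infer that the divisor is left to be chosen after the data and that the correction controls nothing. The document does not support this. A condensed article commonly leaves the list of comparisons, the alpha and the unit of correction to the full analysis plan, which is not shown. Bonferroni also stays valid, and becomes stricter, if every test run is counted, and nothing in the text says that tests will go uncounted. Holm would not cure an open list either, since it needs the same count.

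**Conclusion.** The point holds as a minor improvement. Within whatever set of tests the full plan defines, Holm dominates the stated single-step Bonferroni: the same familywise guarantee, never fewer rejections, and about 1 to 10 percentage points more power per real effect as the number of real effects rises from 10 to 65 of 75. These sizes rest on assumptions that the article does not supply: alpha 0.05, 75 independent tests, and 70 to 80% power under Bonferroni. With moderate correlation the gain is similar or slightly smaller.

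The tests are secondary to a descriptive aim, and keeping Bonferroni would not invalidate any result. Whether the list of comparisons is closed cannot be judged from the article.

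**What to change.** In the Bauer section, replace Bonferroni's correction by Holm's step-down procedure over the same set of chi-square tests. State that every comparison run is counted, including any pairwise contrasts between specialties or procedures, and that pairwise tests are not left unadjusted after a significant global test.

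The cost is one sentence and a trivial change of code; no new data are needed. If simultaneous confidence intervals are wanted for some comparisons, Bonferroni intervals can still be reported for them, with a note that they may not match Holm's decisions exactly.

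### The plan names chi-square tests and logistic regression without saying how hospital is handled; p-values can be too small for exposures that concentrate by hospital

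*Protocol article*

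**What the plan says.** The Study design and ethics section states that "SNAP-1 was a multicentre observational study". Eligibility is set by hospital: "All adult (≥18 years) patients in participating hospitals undergoing any type of surgery or procedure under anaesthesia" could enter on the two study days. The abstract reports that "Preliminary analyses indicate that over 15,000 patients were recruited across the UK".

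The Bauer questionnaire section of the analysis plan names the inferential methods. Responses are analysed "using chi-square testing with Bonferroni’s correction to compare outcomes between categories". The examples given are specialty and operative procedure (separately for ambulatory and inpatient surgery) and urgency. A further comparison, within surgical categories, sets questionnaires given on the day of surgery against those given the day after. Univariate analyses of patient factors follow, and then "Logistic regression will be used to determine independent risk factors for the adverse outcomes". Whether to run subgroup regressions depends on variable type, events per variable and sample size.

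Sites appear in the analysis plan in two places only. One is the recruitment report ("The total number of sites that participated (broken down by country) will be presented"). The other is the local follow-up of possible awareness cases, in the modified Brice questionnaire section. Clustering, a hospital effect, GEE and robust variances are not mentioned.

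**The concern.** Patients in one hospital share a department and its local practice, and satisfaction with anaesthesia care may plausibly differ between departments. If the outcome is correlated within hospitals and the exposure also concentrates in certain hospitals, a test that treats patients as independent understates the variance of the difference and rejects too often. Bonferroni correction does not repair this. It lowers the threshold for the number of tests and leaves the variance inside each test unchanged.

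Several planned comparisons could be affected:
- Specialty and operative procedure can gather in specialist centres.
- For inpatients, who could be approached at any time within 24 h, day of surgery versus next day may follow local team habits.
- The objectives also list procedural factors, and the dataset includes seniority of the anaesthetist and site of induction.

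A second issue applies even where the variance is right. A factor called an independent predictor may partly stand for the hospital in which it is common, unless hospital is in the model. At stake is which associations are reported as real. The raw counts and percentages do not change.

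**Working it through.** **No figure to reproduce.** The article gives no power, significance level, effect size, ICC or number of hospitals, and the target ("The target recruitment rate for the study was 7,500 patients") comes without inputs. The check therefore asks how far a nominal 5% test drifts under stated assumptions.

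**Inputs**
- From the document: about 15,000 patients recruited. The number who completed questionnaires is not given.
- Assumed: 200 hospitals, so m = 15,000 / 200 = 75 patients each.
- Assumed: outcome ICC (ICC_y) 0.01 to 0.05.
- Assumed: exposure ICC (ICC_x) 0 for a factor spread evenly over hospitals, 0.1 to 0.3 for one partly concentrated, 1 for one fixed by hospital.
- Simulation only: 10% event rate, 30% exposed.

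**Formulas**
- Design effect: DE ≈ 1 + (m − 1) × ICC_x × ICC_y
- True two-sided error of a nominal 5% test: 2 × [1 − Φ(1.96 / √DE)]

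**Worked cases (m = 75)**
- ICC_x 0.1, ICC_y 0.01: DE = 1 + 74 × 0.001 = 1.074; √DE = 1.036; error 5.9%.
- ICC_x 0.3, ICC_y 0.05: DE = 1 + 74 × 0.015 = 2.11; √DE = 1.453; error 17.7%.

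**Check by simulation.** Pooled two-proportion chi-square test, beta-binomial outcome, 200 × 75 patients, 4,000 runs per cell. The Monte Carlo standard error near 5% is √(0.05 × 0.95 / 4,000) = 0.34 percentage points.

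| Exposure | ICC_y 0.01: formula / simulated | ICC_y 0.05: formula / simulated |
|---|---|---|
| Same proportion in every hospital | – / 4.6% | – / 4.5% |
| ICC_x 0 | 5.0% / 5.2% | 5.0% / 5.7% |
| ICC_x 0.1 | 5.9% / 6.2% | 9.4% / 9.3% |
| ICC_x 0.3 | 7.6% / 7.3% | 17.7% / 16.6% |
| ICC_x 1 (hospital-level) | 13.7% / 13.6% | 36.6% / 35.8% |

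Formula and simulation agree closely. The rows for ICC_x 0.1 and 0.3 fit the partly concentrated exposures, and the simulated error there runs from 6.2% to 16.6%.

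**Sensitivity to cluster size**, by formula, from (ICC_x 0.1, ICC_y 0.01) to (ICC_x 0.3, ICC_y 0.05):
- m = 150 (100 hospitals): DE 1.149 to 3.235; error 6.8% to 27.6%.
- m = 50 (300 hospitals): DE 1.049 to 1.735; error 5.6% to 13.7%.
- m = 25 (for example, one third of the 75 patients analysed within a surgical category): DE 1.024 to 1.36; error 5.3% to 9.3%.

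The last line matters because the plan runs several comparisons within ambulatory, inpatient or surgical categories, where each hospital contributes fewer patients.

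**The case against.** The strongest reply is that this is a condensed article. It does not specify the logistic model, and a hospital term or robust variance is a detail that a fuller plan could hold. That stands for the regression: a reader might infer that ordinary logistic regression without hospital is planned, but the text neither says so nor excludes a hospital term. It stands less well for the chi-square test. That test is a named choice, its standard form has no place for a hospital term, and the Background says that the paper describes the analysis plan.

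A reader might also infer that p-values are too optimistic throughout, with error rates of 11% to 42%. Those figures follow from 50 to 100 patients per hospital and an ICC of 0.01 to 0.05, but they hold only for an exposure fixed by hospital or for inference on an overall proportion. The Bauer section names no hospital-level exposure and tests no overall proportion. For factors such as age or ASA grade, if they vary mainly within hospitals, the pooled test is close to nominal or slightly conservative.

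Nor do the documents support the claim that intervals on the benchmark percentages will be too narrow, because the article plans counts, percentages and ranges and mentions no confidence intervals. All UK NHS hospitals with anaesthetic departments were invited and the article speaks of a majority being reached, so a design effect that treats hospitals as a small sample from a large population would also overstate the uncertainty of a national figure.

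Finally, the stated main focus is descriptive and no primary hypothesis test is named. That limits the consequence.

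**Conclusion.** The point holds in a limited form. Patients are nested in hospitals, a test that assumes independence is named, and no handling of hospital is stated for it or for the regression. For exposures partly concentrated by hospital, the true error of a nominal 5% test is about 6% to 17% under the central assumptions. It is lower where few patients per hospital enter a comparison and higher if there are fewer, larger hospitals. For patient factors spread evenly over hospitals the error is about 5%, and what remains is possible confounding by hospital of odds ratios presented as independent effects.

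The ICCs, the number of hospitals and the number of completers are not in the document. The direction of the effect is therefore better supported than its size, and the degree to which any named exposure actually concentrates by hospital is unknown. This is a cheap improvement and not a condition for the study's main descriptive results.

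**What to change.** State in the analysis plan, or confirm that the full plan already states, the following:
- Replace the plain chi-square test with a cluster-adjusted version, either Rao-Scott or a GEE-based test, with hospital as the cluster. Keep the Bonferroni correction on top.
- Fit the logistic models with a hospital random intercept, or with GEE or cluster-robust variance. The last two correct the standard errors but do not adjust for confounding by hospital. A random intercept does so only in part, so where that confounding is the worry, also separate the within-hospital from the between-hospital effect of the factor.
- If intervals are put on the national benchmark percentages, use cluster-robust variances.

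No new data should be needed. The awareness follow-up requires the core team to know the site at which each patient was anaesthetised, so hospital should be available for every case. The cost is a few sentences in the plan, slightly more analysis work, and somewhat larger p-values or wider intervals for exposures that concentrate by hospital.
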